#### Data Management

All registered participants’ information was deidentified and given a unique identification number. This identification number was used on all data collected. All contact information of potential participants collected via in-person recruitment or online platforms was stored electronically and password protected. All survey data, whether completed in-person or remotely, were collected via a secure online link and stored electronically. Physiological data were initially recorded on paper and entered into an electronic database. fNIRS and MoCA assessments were conducted in person, and the resulting scores were entered and stored electronically. Blood samples were collected during in-person visits, deidentified, and immediately sent to accredited laboratories for analysis. The results were then stored electronically by the respective laboratories. All electronic records were stored on a secure institutional server, which was protected by password access and restricted to authorized personnel only. All personal information of potential or enrolled participants will be kept a maximum of 5 years before being discarded. The research data used in the publication will be kept for a maximum of 10 years before being discarded. If participants provide informed consent for future studies, their biological samples will be securely stored for a maximum of 10 years. Otherwise, all biological materials will be discarded immediately after the analyses for this study are completed.

#### Statistical Analysis

The primary analysis, intention-to-treat, will be conducted using a linear mixed effects model with overall WHOQOL score as the dependent variable and the interaction effect of intervention allocation and time as the independent variable. Domain-specific scores will also be analyzed. To address potential bias arising from missing data due to attrition or incomplete responses, our primary longitudinal analyses will employ linear mixed-effects models, which are robust to unbalanced data structures and can handle missing observations under the missing-at-random assumption. While listwise deletion may be used for cross-sectional comparisons or descriptive analyses, this will be clearly indicated. Secondary outcomes will be analyzed using similar methods. These analyses will be conducted at 6-month follow-up to investigate the effectiveness of the intervention as well as post-intervention behavioral maintenance at 12 months. Sensitivity analysis using the per-protocol approach will also be carried out. Baseline characteristics of participants who discontinued or were lost to follow-up will be compared to those who completed the study to investigate differential dropout between intervention and control groups.

Due to potential imbalances between the groups, further analysis techniques, such as adjustment or matching of baseline characteristics, will be used in the difference-in-difference analysis. Specifically, we will adjust or match on key baseline covariates (eg, age, gender, years of education, marital status, and housing type) to improve group comparability at baseline in case of any imbalance despite randomization. This approach improves covariate balance and enhances the comparability of groups prior to applying linear mixed models for outcome analyses. Conducting both intention-to-treat and per-protocol analyses for this behavioral intervention allowed comparison of the results and provided a comprehensive understanding of the treatment effect. All evaluations were and will be performed using a 2-sided test at the 5% level of significance.

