## Methods

### Study Design

This UCF intervention was a parallel group, 2-arm, pragmatic waitlist randomized trial with 1:1 allocation ratio to either intervention or waitlist control. The intervention group completed the first 24-week UCF program, followed by a 24-week observation period. The control arm served as a waitlist group, receiving no intervention during the initial 24 weeks but undergoing the same intervention in the following 24 weeks after the intervention group completed. Participants in both arms completed assessment at baseline, 6-month, and 12-month follow-up. We reported using the standard protocol items: recommendation for interventional trials (Standard Protocol Items: Recommendations for Interventional Trials [SPIRIT]) checklist (Checklist 1) [29].

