### Sample Size

This study aimed to compare the QOL between the treatment and waitlist control participants, using a 1:1 allocation ratio. Based on a prior study of the overall WHOQOL measure, if the true difference-in-differences estimate between experimental and control means is 4.93 with a standard deviation of 9.29 [46], a sample of 57 intervention and 57 control subjects is required to reject the null hypothesis based on a 2-tailed significance level of 5% and power of 80%. We inflated the sample by 20% to account for dropouts and the potential loss of participants due to noncompliance and faulty measurements. Accounting for all these factors, the total sample size required for 2 arms is 138 participants.

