## Results

This randomized controlled trial (RCT) commenced in April 2024, with the intervention group undergoing the intervention for the first 24 weeks, which ended in September 2024. Prior to the start of the data collection and intervention, participants were screened for eligibility, and informed consent was obtained. A total of 137 participants were enrolled, with 67 randomized to the intervention group and 70 to the control group. Baseline data were collected in March 2024, and the 6-month follow-up was completed in September 2024. The waitlist control group began the 24-week UCF intervention in late September 2024 and completed it in April 2025, with a 3-week break over Christmas, New Year, and Lunar New Year period. Data collection for the 12-month follow-up concluded in May 2025. Analysis of the baseline and 6-month follow-up data is currently ongoing. The participant timeline is presented as a flowchart in Figure 1.

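### The 12-month maintenance analysis reuses the allocation-by-time contrast after the waitlist arm has completed the same programme, so it cannot measure maintenance; the 6-month comparison is unaffected

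*Protocol article*

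**What the plan says.** The Statistical Analysis section of the protocol article gives one primary model, a linear mixed model for the overall WHOQOL score with "the interaction effect of intervention allocation and time as the independent variable". Secondary outcomes are to be handled similarly. The section then assigns this work to two questions at two visits: "These analyses will be conducted at 6-month follow-up to investigate the effectiveness of the intervention as well as post-intervention behavioral maintenance at 12 months".

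Study Design describes the control arm as untreated for the first 24 weeks and then "undergoing the same intervention in the following 24 weeks after the intervention group completed". Over that second period the intervention arm is only observed. Both arms are assessed at baseline (T0), 6 months (T1) and 12 months (T2).

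The Results section gives the dates. The intervention arm finished in September 2024. "The waitlist control group began the 24-week UCF intervention in late September 2024 and completed it in April 2025". Collection of the 12-month data ended in May 2025.

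**The concern.** A between-arm difference-in-differences estimates a programme effect only while one arm is untreated. That holds from T0 to T1. At T2 both arms have had UCF, one recently and one some time ago, so the interaction at T2 no longer contrasts UCF with no UCF.

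Maintenance is a stated aim of the 12-month visit. If the planned analysis is followed, a fully sustained benefit gives an expected null, and ordinary fading gives a negative estimate that could be taken for harm. A null would also be expected if UCF had never worked in either arm, so the T2 contrast alone cannot tell a lasting benefit from no benefit.

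**Working it through.** **Inputs.** Sample Size: "if the true difference-in-differences estimate between experimental and control means is 4.93 with a standard deviation of 9.29", with a two-sided 5% test and 80% power. Results: 67 participants randomised to intervention and 70 to waitlist.

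**The plan's own figure.** "a sample of 57 intervention and 57 control subjects is required". The normal formula gives n = 2 x (1.960 + 0.842)^2 x 9.29^2 / 4.93^2 = 55.7, so 56 per arm. The exact t calculation gives 57 per arm (power 80.2%). The stated figure is reproduced, so 4.93 and 9.29 are taken as the design values.

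**At 6 months.** The waitlist arm is untreated, so the expected contrast is 4.93 - 0 = 4.93. With 67 and 70 participants the t calculation gives power of about 87%.

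**At 12 months.** Let r be the share of the intervention arm's gain still present at T2, and W the waitlist arm's fresh gain from its own programme. Time trends common to both arms cancel, so

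expected T2 contrast = r x 4.93 - W.

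*Equal gains, W = 4.93 (an assumption).* The standard error is 9.29 x sqrt(1/67 + 1/70) = 1.588. This takes the 6-month SD as valid at 12 months and ignores dropout. Normal two-sided test at 5%:

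| Share maintained | Expected T2 contrast | Significant in favour of the intervention arm | Significant against it |
|---|---|---|---|
| 100% | 4.93 - 4.93 = 0.00 | 2.5% | 2.5% |
| 75% | 3.70 - 4.93 = -1.23 | 0.3% | 11.8% |
| 50% | 2.465 - 4.93 = -2.465 | under 0.1% | 34.2% |
| 25% | 1.23 - 4.93 = -3.70 | about 0% | 64.4% |
| 0% | 0 - 4.93 = -4.93 | about 0% | 87.4% |

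With 57 per arm, the last column becomes 29.3% at half maintained and 80.9% at none. A simulation of 4,000 trials under full maintenance (67 and 70 participants, assumed within-person correlation 0.5) gave a mean 6-month estimate of 4.94, significant in 87.6%. The mean 12-month estimate was -0.02, significant in 5.2%, which is close to the type I error rate.

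*Unequal gains.* Suppose the waitlist arm gains half as much, W = 2.465. Full maintenance then gives 4.93 - 2.465 = +2.465, half gives 2.465 - 2.465 = 0, and none gives -2.465. A T2 contrast of zero thus fits full maintenance with equal gains, half maintenance with a half-size waitlist gain, or no effect in either arm (0 - 0). One number cannot separate r from W.

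**Within-arm alternative.** In the intervention arm the expected change from T1 to T2 is (r - 1) x 4.93, which is 0 with full maintenance and -4.93 with none, plus any time trend. It does not involve W, so it addresses maintenance directly, though without a concurrent control.

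**The case against.** The strongest reply is that the wording does not force the between-arm reading. Maintenance most naturally describes what happens in the intervention arm during its observation period, and a fitted allocation-by-time model can supply that arm's T1-to-T2 and T0-to-T2 changes. An article condenses a fuller plan, and the crossover is openly described. It is true that the planned model can yield the right quantity. However, the article names the interaction and carries the same analyses to 12 months. It names no within-arm contrast and no time-varying exposure. The limitations in the Discussion mention attrition for longer-term outcomes but not the loss of the untreated comparator. The economic evaluation, by contrast, confines its QALYs to the 24-week period. The problem is thus a stated analysis that does not fit its stated aim, rather than an omitted detail.

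A second reply is that with exactly equal gains the T2 contrast equals the loss since month 6, so zero would be good news. The algebra is right. But the plan does not state the equal-gain assumption, the documents give no waitlist-arm effect, and that arm's delivery included a 3-week break. A non-significant result would not in any case demonstrate that nothing was lost.

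A reader might also infer that the primary result is compromised: that no primary time point is fixed, or that a single linear time term over three visits would cancel the effect. The documents do not support this. The Statistical Analysis section ties effectiveness to the 6-month follow-up, and no section specifies linear time or pools T1 with T2.

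**Conclusion.** The 12-month maintenance analysis is wrong as written. With the waitlist arm treated between T1 and T2, the between-arm contrast at T2 estimates retained minus fresh effect, which is not maintenance. The values 0, about -2.47 and -4.93 for full, half and no maintenance rest on the design effect of 4.93 and on an equal gain in the waitlist arm. The rejection probabilities also assume an SD of 9.29 at 12 months and no dropout. The main conclusion needs none of these figures: it follows from the crossover alone. The documents give the end of 12-month data collection but not its start, so just finished describes the waitlist arm only approximately. By the calendar, the intervention arm's gap from September 2024 may be somewhat longer than six months. Neither point changes the conclusion, and the 6-month comparison stands.

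**What to change.** - State that the allocation-by-6-month contrast is the only randomised estimate of effectiveness. If all three visits enter one model, enter time as categorical.
- Define 12-month maintenance as the intervention arm's within-arm changes from T1 to T2 and from T0 to T2, with confidence intervals, labelled non-randomised and uncontrolled.
- Report the waitlist arm's T1-to-T2 change as a supportive pre-post replication.
- If a T2 between-arm contrast is shown, label it early versus delayed UCF, and do not present it as effectiveness or maintenance.
- Add the loss of the untreated comparator after 6 months to the limitations.

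The cost is a change of wording. All the data needed are already collected, and the article reports that analysis of the baseline and 6-month data is still under way. The sponsor gives up a randomised claim about maintenance, which this design cannot support. The within-arm changes remain open to time trends and selective dropout, and the label should make that clear.

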**Methods:**

We conducted a parallel group, 2-arm pragmatic waitlist randomized trial with a 1:1 allocation, in which participants were randomized into either the intervention or waitlist control arm. Community-dwelling participants aged 50-85 years, without any mobility issues, were recruited. Participants in the intervention arm commenced the 24-week UCF program, while waitlist control participants received no intervention during this period. The primary (World Health Organization Quality of Life−brief version) and secondary outcomes were collected at baseline, 6th month, and 12th month after the intervention group completed the trial. Secondary outcomes include objectively measured physiological outcomes, cognition, frailty, and self-reported psychosocial outcomes. Intervention effects were estimated using mixed-effects difference-in-differences regression to account for repeated measurements.

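### If baseline imbalance is seen, the plan allows matching before the main mixed model; ordinary matching drops randomised participants, which conflicts with the stated intention-to-treat analysis and costs power

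*Protocol article*

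**What the plan says.** The Statistical Analysis section opens with the primary analysis: "The primary analysis, intention-to-treat, will be conducted using a linear mixed effects model with overall WHOQOL score as the dependent variable". The intervention effect is the interaction of allocation and time.

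Its second paragraph adds that, because the groups may be unbalanced, "further analysis techniques, such as adjustment or matching of baseline characteristics, will be used in the difference-in-difference analysis". It then specifies: "we will adjust or match on key baseline covariates (eg, age, gender, years of education, marital status, and housing type". The stated purpose is "to improve group comparability at baseline in case of any imbalance despite randomization", and the step is said to be one that "enhances the comparability of groups prior to applying linear mixed models for outcome analyses".

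Two other places show which analysis this touches. The Methods part of the Abstract says "Intervention effects were estimated using mixed-effects difference-in-differences regression to account for repeated measurements". The Discussion, in its limitations paragraph, says that the linear mixed models are the means of obtaining the difference-in-difference estimates. In the Statistical Analysis section only the per-protocol analysis is called a sensitivity analysis.

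**The concern.** In a randomised trial, baseline differences between arms arise by chance, and the standard error of the treatment effect already allows for them. No repair step is needed before the model is fitted. Adjustment for prognostic covariates can still be worthwhile, because it gains precision and leaves the randomised set whole.

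Matching is different. In its ordinary form, each participant in one arm is paired with a similar participant in the other, and those without a partner are set aside. The analysed set is then no longer everyone randomised, and the effect refers to a matched subset that the protocol does not define. If this happens before the model that yields the main effect, it contradicts the intention-to-treat label in the same section. It also shrinks a sample that has little spare power once the planned losses occur.

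The words leave two quite different routes open, and a reader cannot tell which participants will stand behind the primary result.

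**Working it through.** **1. The protocol's own sample size.** Inputs from the Sample Size section: difference 4.93, SD 9.29, two-sided 5%, power 80%, 20% inflation.

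- Normal approximation: n per arm = 2 × (1.960 + 0.842)² × (9.29/4.93)² = 2 × 7.85 × 3.55 = 55.7, so 56.
- Two-sample t-test: 56.7, so 57, with power 80.2%. This matches the stated 57.
- Inflation: 57 × 1.2 = 68.4, so 69 per arm and 138 in total. This matches the stated total.

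The point does not rest on any sample-size error.

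**2. The least that 1:1 matching can remove.** The Results section gives 67 and 70 randomised. At most 67 pairs can form, so 137 − 2 × 67 = 3 participants are lost even if every match succeeds.

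**3. A plausible loss.** The protocol names no matching method, so this step is assumed: 1:1 propensity matching on five independent covariates, caliper 0.2 SD of the logit, simulated under randomisation.

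- With 55 per arm, 41 pairs are kept (75%) under greedy matching and 44 (80%) under optimal matching.
- With 67 against 70, 53 pairs (79% of the smaller arm) are kept under greedy matching and 57 (85%) under optimal matching. The latter is about 113 of 137 people.

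A loss of 15% to 25% is therefore typical under these assumptions. I carry 15% to 30%.

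**4. Effect on power.** Two-sample t-test, two-sided 5%, standardised difference 4.93/9.29 = 0.531. Evaluable numbers after 20% dropout are 67 × 0.8 = 53.6, or averaged over both arms 137 × 0.8 / 2 = 54.8, taken as 55.

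| Per arm before matching | No matching loss | 15% lost | 20% lost | 30% lost |
|---|---|---|---|---|
| 67 (no dropout) | 86.2% | 80.2% | 77.7% | 72.0% |
| 55 | 78.8% | 71.9% | 69.2% | 63.3% |
| 53.6 | 77.7% | 70.7% | 68.0% | 62.1% |

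Keeping the full 67 and 70 with no dropout gives 86.9%. These figures treat the matched set as a smaller sample with the same SD. They give matching no credit for removing covariate variation, but adjustment on everyone would capture that gain without losing anyone.

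**5. How often the trigger would fire.** No threshold is stated. With five independent covariates, the chance that at least one differs at p < 0.05 is 1 − 0.95⁵ = 22.6%, and at p < 0.10 it is 1 − 0.90⁵ = 41.0%.

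**6. Type I error.** Null simulations used five covariates with coefficient 0.2 each, the same caliper, and a trigger at p < 0.05 or p < 0.10 (4,000 runs per setting, simulation error about 0.3 percentage points).

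- Unadjusted model, switching to adjustment when triggered: 4.3% to 5.3%.
- Unadjusted model, switching to matching when triggered: 3.4% to 4.8%.
- Smallest p-value of the unadjusted, adjusted and matched analyses: about 8% (7.4% to 8.9% across all simulations run, including some with other covariate strengths).

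**The case against.** The strongest reply is that the first paragraph already fixes the primary model without covariates, and that the second offers further techniques, which can be read as supplementary. The text is ambiguous enough for that reading. Against it stand the stated order (matching first, mixed model second), the Abstract and Discussion, which make the difference-in-differences mixed model the effect analysis, and the absence of any sensitivity label on this step. The ambiguity itself needs resolving.

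It is also fair to say that the covariate list, the imbalance threshold and the matching algorithm are details a journal article may leave to a fuller plan. I make no finding of their absence. The point is the route that the article does state.

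Four stronger readings are tempting but not supported:

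- *That adjusting also breaks intention-to-treat.* It does not. Adjustment keeps everyone who has covariate data.
- *That the imbalance rule inflates the type I error.* Step 6 shows that it does not. The figure near 8% requires picking by outcome, which no section plans.
- *That the choice was made after outcomes were seen.* The Results section says that analysis of baseline and 6-month data is under way. That describes the reporting date, not when the plan was set.
- *That housing type was not collected because Table 2 omits it.* The table is headed as an overview and also omits serum creatinine (Biomarkers section) and self-reported health care use (Economic Evaluation section). Nothing follows from its silence.

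**Conclusion.** The point holds for the matching branch only. As written, observed imbalance may lead to matching before the model that gives the intervention effect. Ordinary matching that discards unmatched people would then conflict with the intention-to-treat primary analysis.

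The certain loss under 1:1 matching is small, 3 of 137. Under an assumed 0.2-SD caliper, roughly 75% to 85% of possible pairs survive. With 20% dropout, a matching loss of 15% to 30% takes power from about 78%-79% to about 72%-62%. With no dropout and a 15% loss, power would still be about 80%. All the power figures depend on the assumed dropout and match rate. A matching method that keeps everyone, for instance by weighting, would not remove participants, but the article does not say that one is intended.

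This is a fault of specification and efficiency, with no evidence of biased testing. It is worth correcting because it decides which participants the primary estimate describes.

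**What to change.** State one primary model: the linear mixed model on all randomised participants, with a closed set of baseline covariates (for example age, gender, years of education and marital status) entered whatever balance is observed. Report the same model without covariates as a sensitivity analysis. Delete matching, or keep it only as a labelled sensitivity analysis. Remove the condition that makes adjustment depend on imbalance.

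Keeping the model without covariates as primary, with adjusted and matched results labelled as sensitivity analyses, would also remove the conflict. Fixed adjustment is preferable for the precision it can bring.

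The cost is a change of wording, a few degrees of freedom, and the freedom to choose the model later. No new data are needed. The change should be made and dated before the ongoing analysis is completed.
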